### Trial status

The first patient was included in January 2013. An interim analysis was performed in September 2015 including 40 patients after two years of participation [31]. The interim analysis evaluated the rates of decline in kidney function between the two groups to ensure the safety of the study drug and found no difference between the two groups. In November 2017 a total of 142 patients were active in the study and 41 baseline biopsies had been performed. Inclusion is expected to be complete by 2018.

## Discussion

Long term kidney graft survival is a key issue in transplant medicine. Chronic CNI nephrotoxicity contributes to late allograft loss [3]. There is increasing evidence, that aldosterone plays a role in detrimental processes beyond fluid and sodium homeostasis e.g. inflammation and fibrosis, thereby possibly contributing to allograft failure [7]. Several animal studies have shown an effect of MR antagonism in reducing CNI nephrotoxicity [30]. The few available human studies addressing this hypothesis have been underpowered or focused on short term effects [19, 22]. This study aims to provide sufficiently powered evidence regarding the effect of long term MR antagonism on GFR and the development of kidney fibrosis in prevalent kidney transplant patients.

Concerns have been raised regarding MR antagonism in patients with impaired renal function due to the risk of hyperkalemia, which is a potentially lethal side-effect. In the wake of the Randomized Aldactone Evaluation Study (RALES) - a randomized, clinical trial investigating the effect of spironolactone in patients with congestive heart failure and serum creatinine below 221 μmol/L - there was a significant increase in hospitalizations due to hyperkalemia from 2.4 to 11.0 per 1000 patients [32]. The risk of hyperkalemia increases as GFR deteriorates. One safety study of MR antagonist eplerenone 25 mg/day for 8 weeks in 31 kidney transplant patients found a significant increase in plasma potassium during eplerenone treatment, however there was only one incidence of moderate hyperkalemia (> 5.5 mmol/L) and no patients were withdrawn from the study due to hyperkalemia. It was concluded, that MR antagonism is safe in kidney transplant patients with a GFR > 30 mL/min, but warrants close monitoring of plasma-potassium [33].

Another concern regarding MR antagonism is the observation that plasma creatinine levels tend to increase at the initiation of therapy. This effect has also been observed in studies of MR antagonism in chronic kidney disease [34]. In RALES, spironolactone significantly increased the occurrence of worsening renal function - defined as a reduction of eGFR> 30% - however, this did not impact the relative mortality risk in this group. Interestingly, worsening renal function was associated with an increased adjusted mortality risk in the placebo group, but not in the spironolactone group [35]. Although the increase in plasma creatinine is reversible when MR antagonists are discontinued, worsening renal function poses a diagnostic challenge with several possible etiologies in the kidney transplant population (e.g. acute rejection, post-renal obstruction, BK-virus nephropathy etc.). If in doubt, MR antagonists should be discontinued and appropriate diagnostic measures performed.

Despite potential pitfalls using MR antagonists in kidney transplant patients, evidence from animal and small human studies indicate a potential for improving long term allograft function. This study is, to our knowledge, the first to investigate the effect of MR antagonism on long term allograft function in adult kidney transplant patients in a prospective, randomized fashion. Results will contribute to current evidence and possibly influence the future management of kidney transplant patients with regards to improving long term allograft survival.

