**Discussion:**

Long term allograft survival remains a key issue in renal transplantation, partly due to calcineurin inhibitor induced nephrotoxicity. Evidence from animal- and small human studies indicate a beneficial effect of mineralocorticoid receptor antagonism on renal function and fibrosis. This study aims to test this hypothesis in a sufficiently powered randomized clinical trial. Results might influence the future management of long term allograft survival in renal transplantation.

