### Objectives and design

The SPIREN trial is an investigator initiated nationwide, multicenter, randomized, double-blind, placebo-controlled clinical trial designed to test the hypothesis that addition of the MR-antagonist spironolactone to standard therapy in prevalent kidney transplant patients will improve long term kidney function and reduce allograft fibrosis.

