## Methods

One hundred seventy kidney transplant patients will be included from four Danish hospitals covering all Danish renal transplant centers (Odense, Copenhagen and Aarhus). Patients are recruited from outpatient clinics in the Departments of Nephrology at Odense University Hospital, Kolding Hospital, Rigshospitalet, Copenhagen and Aarhus University Hospital, respectively. Eligibility criteria are listed in Table 1.

**Table 1 Tab1:** Eligibility criteria

Inclusion criteria	Exclusion criteria
Age > 18 years	Former intolerance of spironolactone
Tacrolimus/cyclosporine treatment	Potassium binder or digoxin treatment
Proteinuria < 3 g/day	Pregnancy or planned pregnancy
Creatinine clearance ≥30 mL/min	Clinically relevant organic, systemic or psychological disorder
Plasma potassium < 5.5 mmol/L	Expectation of non-compliance
Negative pregnancy test at inclusion for women of childbearing potential and adequate contraception throughout the trial	

Wide eligibility criteria have been chosen to obtain a high generalizability of the results. This study includes renal transplant patients with a stable kidney function at the time of inclusion. Even in stable patients, a gradual deterioration of renal function is expected. Previous studies have found an average rate of decline of glomerular filtration rate in of 1–3 mL/min/year [23–26]. Hence, we chose a follow up of 3 years.

Patients are randomized 1:1 to spironolactone (Spirix®) or placebo for three years. Initial dosage is 25 mg once daily, which is doubled after three months, if tolerated well. At inclusion and yearly hereafter a standard workup is performed including chrome-EDTA clearance, 24-h urine collection, electrocardiogram, 24-h ambulatory blood pressure measurement and blood- and urine samples (Fig. 1). Anonymized samples are stored at − 80 °C until analyses. In a subgroup (*n* = 50) graft biopsies will be performed at inclusion and after two years. All registrered variables are listed in Table 2.

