### Sample size

Assuming a standard deviation in chrome-EDTA clearance of 10 mL/min, a sample size of 126 patients (63 in each group) will be able to detect a difference in chrome-EDTA clearance of 5 mL/min between the groups with 80% power and a significance level of 0.05. With an expected dropout rate of 15%, the planned total was set to 170 patients.

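### The article calls the trial sufficiently powered for kidney fibrosis as well as GFR, but its only power calculation is for GFR and fibrosis is measured in a planned 50 patients

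*Protocol article*

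**What the plan says.** The power claim that names fibrosis is in the Discussion of the protocol article, where the study aims to provide "sufficiently powered evidence regarding the effect of long term MR antagonism on GFR and the development of kidney fibrosis". The Discussion paragraph of the Abstract reaches fibrosis by reference: it first mentions renal function and fibrosis together, then states "This study aims to test this hypothesis in a sufficiently powered randomized clinical trial". Objectives and design sets out the hypothesis that adding spironolactone "will improve long term kidney function and reduce allograft fibrosis". That section says nothing about power.

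The calculation under Sample size covers one outcome: "a sample size of 126 patients (63 in each group) will be able to detect a difference in chrome-EDTA clearance of 5 mL/min", with an SD of 10 mL/min, 80% power, a significance level of 0.05 and a planned total of 170 to allow for 15% dropout.

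Fibrosis is listed as a secondary endpoint under Outcome. Methods gives the number of patients and the timing: "In a subgroup (*n* = 50) graft biopsies will be performed at inclusion and after two years". Trial status reports that by November 2017 "41 baseline biopsies had been performed", with inclusion still open. The article gives no SD, target difference or power for fibrosis.

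**The concern.** A secondary endpoint needs no power calculation, and a lack of one would be no fault. The problem is that the article asserts adequate power for fibrosis while its own design figures give no support for it. The 126 or 170 patients behind the GFR calculation will mostly have no fibrosis measurement. A two-year comparison that uses the baseline value also needs both biopsies from each patient.

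What is at stake is how a non-significant fibrosis result would be read. Under a label of adequate power, readers may take it as evidence that spironolactone does not affect fibrosis. The article's Background sets aside the null findings of a 24-patient paediatric trial, fibrosis included, as underpowered, so the same standard should apply to its own biopsy subgroup.

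**Working it through.** **Inputs.** From Sample size: difference 5 mL/min, SD 10 mL/min, power 80%, alpha 0.05 (taken as two-sided, which reproduces the stated figure), dropout 15%. From Methods: 50 biopsied patients, 1:1 allocation. No fibrosis SD is given, so fibrosis differences are expressed in SD units.

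**1. The plan's own figure.** n per arm = 2 × (1.960 + 0.842)² × (10/5)² = 62.8, rounded up to 63, so 126 in total. This reproduces the article (the t-test version gives 64 per arm). The standardised effect is 5/10 = 0.5 SD.

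**2. Evaluable biopsy pairs.** All 50: 25 per arm. With 15% dropout: 50 × 0.85 = 42.5, about 42 pairs, 21 per arm. Both assume that the subgroup splits evenly between arms. The 15% is stated for the trial as a whole, and applying it to the two-year biopsy is an assumption.

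**3. Unadjusted comparison.** The normal approximation to the difference detectable with 80% power is 2.802 × √(2/n). This gives 2.802 × √(2/25) = 0.79 SD and 2.802 × √(2/21) = 0.86 SD. The t-test values, slightly larger, are in the table. The 95% CI half-width is t(0.975, 2n − 2) × √(2/n).

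| Pairs | Detectable at 80% power (t) | Power at 0.5 SD (t) | 95% CI half-width |
|---|---|---|---|
| 50 | 0.81 SD | 41% | 0.57 SD |
| 42 | 0.89 SD | 35% | 0.62 SD |

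Both half-widths exceed 0.5 SD. Even an estimate of exactly zero would leave a 0.5 SD benefit inside the interval.

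**4. Adjusted for the baseline biopsy.** The residual SD shrinks by √(1 − r²), where r is the correlation between the baseline and two-year values. The article gives no r, so 0.5 and 0.7 are assumed. The factors are √0.75 = 0.866 and √0.51 = 0.714.

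| Pairs | Detectable, r = 0.5 | Detectable, r = 0.7 | Power at 0.5 SD, r = 0.5 | Power at 0.5 SD, r = 0.7 |
|---|---|---|---|---|
| 50 | 0.81 × 0.866 = 0.70 SD | 0.81 × 0.714 = 0.58 SD | about 53% | about 70% |
| 42 | 0.89 × 0.866 = 0.77 SD | 0.89 × 0.714 = 0.63 SD | about 46% | about 62% |

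The adjusted powers use the normal approximation; t-based values are one or two points lower. All stay below 80%. The half-widths shrink by the same factors, to 0.49 and 0.41 SD with 50 pairs and to 0.54 and 0.44 SD with 42.

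**The case against.** The strongest reply is that this is a loose sentence in a design that is otherwise openly labelled. Fibrosis is called secondary, the subgroup size is stated, and Sample size ties power to chrome-EDTA clearance alone, which is normal practice. A rationale for 50 biopsies may exist in the full protocol. The sentence also says only what the study aims to do. Most of this stands, and it makes the point one of wording and reporting rather than of a defective design. It does not rescue the claim, because the article fixes the number of biopsies and still describes the evidence on fibrosis as sufficiently powered.

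The reply also rightly limits several stronger readings:

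- A reader might infer that a null fibrosis result would be uninformative. It would not be: it would count against differences of roughly 0.8 to 0.9 SD or more.
- A reader might take 41 as the final number of biopsies, or infer 26% dropout from 126 out of 170, and so arrive at a still smaller subgroup. The 41 is an interim count with inclusion open, the plan is 50, and the stated dropout is 15%.
- A reader might treat 0.5 SD as the trial's fibrosis target. It is borrowed from the GFR calculation.
- A reader might take 0.9 SD as the limit under any analysis. That figure is unadjusted, and a baseline biopsy is planned.

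The acknowledged sampling error and subjectivity of the fibrosis measures are partly offset by point counting, which the article describes as reproducible, and by a single pathologist. The 24-patient trial is about half the size of the biopsy subgroup and does not by itself show that 50 is too few. Nor does the article say that it will read non-significance as no effect.

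**Conclusion.** The point holds as a mismatch between a stated property and the design. The Discussion says outright, and the Abstract by reference, that the trial is sufficiently powered for fibrosis, and nothing in the article shows this. Without adjustment, 80% power is reached only at about 0.81 to 0.89 SD. At an assumed 0.5 SD, power is about 41% with all 50 pairs and 35% with about 42. Baseline adjustment helps but does not reach 80% at that effect for the correlations considered.

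These results rest on an even split between arms, a two-sided 5% test, and, for the smaller case, the trial's 15% dropout applying to the second biopsy. Power for fibrosis in absolute units cannot be computed from the article. The GFR calculation is unaffected.

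**What to change.** 1. Limit the statement of sufficient power to GFR in the Discussion and in the Discussion paragraph of the Abstract.
2. Analyse the two-year fibrosis percentage adjusted for the baseline biopsy value, and report the between-group difference with a 95% CI. Draw no conclusion of no effect from a non-significant test. If the analysis plan already provides for this, only the wording needs to change.
3. State the detectable difference for that adjusted analysis together with the assumed correlation: about 0.77 SD (r = 0.5) or 0.63 SD (r = 0.7) for about 42 pairs, and 0.70 or 0.58 SD with all 50. The unadjusted 0.89 SD for about 42 pairs can stand beside these for comparison, but should not be given as the precision of the adjusted analysis.

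The cost is a few sentences and one model on data already planned. No extra biopsies are needed. The downside is that the article's claim becomes less favourable.

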## Abbreviations

CNI: Calcineurin inhibitors
GFR: Glomerular filtration rate
MR: Mineralocorticoid receptor
RALES: The Randomized Aldactone Evaluation Study
TGF-β: Transforming growth factor β
